**Table 1 Tab1:**
[figure not shown]
Schedule of enrolment, interventions, and assessments

#### Electronic data collection tool

Data will be captured using an android application developed using Java. Each data collector will use Samsung Galaxy 7 in. tablet with Internet enabled SIM card for data collection and transmission of data from the community to central database server. The application will navigate the data collectors through a step-by-step process while interviewing the pregnant women to collect all required information to be collected at each specific visit. Some validation rules will be set in the application to prevent errors during data collection. Rules will include logical and range checks, uniqueness check and skipping rules as appropriate.

Initially, the Field Implementers will enter all the required registration information of the woman into the system. As soon as the data is uploaded to the server, information will be passed to the separate evaluation team for first follow up visit. Each data collector will need to log into the system using a pre-assigned unique user ID and password. During the first visit, the data collector will download the details of the newly registered pregnant women for her assigned cluster from the central server. This information, filtered according to the geographical area, comes from the registration data collected by the Field Implementers. During the subsequent visits, the app will provide each data collector with a list of women, for whom a follow-up visit is scheduled within seven days. We will use different colour coding to highlight visits that are pending or imminent. To verify physical presence of the data collectors at the households we will record a Geographic Information System (GIS) data point. The system will also generate daily reports of the completed interviews and enrolment and make them available on the online monitoring interface (in real time). At the end of each interview, the data collector will store the data on the local device and then upload the data to the central server after the end of a day’s work. We will maintain a backup copy of the database on a different server.

### Statistical analysis

Data analysis will be by intention to treat. We will conduct analyses at the infant level adjusted for the cluster randomisation. The primary analyses will compare the neonatal mortality rates and their 95% confidence intervals adjusted for clustering and groundwater iron level in each group. Secondary analyses will examine each outcome variable using separate mixed models. We will use Cox proportional hazards mixed models for mortality outcomes and include groundwater iron level as an interaction term in the mortality model. We will use population average Poisson model for other outcomes including preterm, small for gestation and low birth weights. Models will include treatment group as a fixed effect, community-cluster as a random effect to account for the cluster effect. The models will evaluate the impact of the interventions over time by testing for an interaction between time and intervention group. We will conduct analyses to identify the subgroups (based on household wealth, sex of infant and maternal education) that modify the response to the intervention. We will check the model assumptions and make appropriate adjustments to the analysis where necessary. Descriptive analysis will be performed to present the cause of death. We will compare the causes of death by sex of newborn, the time-period of death, and treatment arms (intervention Vs control). χ^2^ test or Fisher’s Exact test after adjusting for cluster effect will be used when appropriate. The economic analysis will estimate the incremental cost per life saved per year of the intervention over standard care. We will use sensitivity analyses of the findings to assess uncertainty in key parameters. Stata V.14 (StataCorp. 2015. Stata Statistical Software: Release 14. College Station, TX: Stata Corp LP.) will be used for all analyses.

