### Sampling frame and sample size

To detect a 25% reduction in neonatal mortality (33 neonatal deaths/1000 live births in control to 24.8 neonatal deaths/1000 live births in the intervention group), with 90% power, 5% two-sided alpha, 1:1 ratio of treatment allocation and intra-cluster correlation coefficient (ICC) of 0.0245, we require 100 clusters (each covering an average of 4000 households), or 50 clusters per treatment group, with a total of 30,000 live births over one year. This sample would allow detection of a 22% relative difference between treatment groups with 80% power. To detect a 30% reduction in preterm delivery from 15% in control compared to 10.5% in the intervention arm, assuming 80% power, 5% level of significance, intracluster correlation of 0.012 for small birth size (Bangladesh DHS data), would require a sample size of 1300/arm or 40 pregnant women from 64 clusters. A smaller sample size of 570 women/arm or 40 pregnant women from 28 clusters is needed to detect a 30% reduction in LBW with the same assumptions. Our cluster is one BRAC PO area that consists of ~ 13,000 people. Assuming a crude birth rate of 23 per 1000 people, 10% loss of pregnancies before birth and 15% loss to follow up each cluster will yield 300 births over 15 months, and this will be sufficient to reach the desired sample size.

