#### Types of information collected

Over the pregnancy and neonatal period, data collectors will collect information regarding household characteristics, reproductive history, pregnancy information, medication history, details about consumption of IFA supplements, current health status, any side effects from the supplements, antenatal care, birth outcome, birth weight, immediate newborn care and neonatal deaths. We will also collect information on exposure to household air pollution and out of pocket expenses for any antenatal and postnatal care seeking (Table 1).

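### The primary mortality comparison makes no use of clusters' earlier neonatal mortality, probably derivable from the reproductive history; adding it is a cheap precision gain whose size depends on an ICC that must first be reconciled

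*Protocol article*

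**What the plan says.** The Statistical analysis section of the protocol article sets the adjustment for the primary outcome: "The primary analyses will compare the neonatal mortality rates and their 95% confidence intervals adjusted for clustering and groundwater iron level in each group". The models have treatment as a fixed effect and cluster as a random effect, and groundwater iron enters the Cox mixed model as an interaction term. Household wealth, infant sex and maternal education appear only as possible effect modifiers. No measure of mortality before the trial is named.

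Under Types of information collected, the article states that "data collectors will collect information regarding household characteristics, reproductive history, pregnancy information, medication history" and further items. The Data collection team section says that this team is separate from those who deliver the intervention. The article does not say what the reproductive history contains.

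The Sampling frame and sample size section aims at a fall in neonatal mortality from 33 to 24.8 per 1000, at 90% power and a two-sided 5% level. The clustering assumption is an "intra-cluster correlation coefficient (ICC) of 0.0245". The resulting size is given as "50 clusters per treatment group, with a total of 30,000 live births over one year". The section also claims 80% power for a 22% relative difference.

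**The concern.** In a cluster trial, part of the variance of each cluster's mortality rate is persistent difference between clusters. A cluster's own earlier mortality measures that part directly. Groundwater iron does so only as far as it happens to track mortality. If the reproductive history gives earlier births and their survival, the covariate costs almost nothing, and leaving it out gives up some precision on the primary outcome.

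Chance imbalance is also involved. Ignoring stratification, the difference in underlying mortality between two randomly chosen sets of 50 clusters has a standard deviation of about 5.2 per 1000 at the printed ICC, and about 1.7 per 1000 at an ICC ten times smaller. The target effect is 8.2 per 1000. Adjustment would remove part of that noise from the estimate.

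**Working it through.** **Inputs from the article (Sampling frame and sample size).** Rates p1 = 0.033 and p2 = 0.0248, so the difference is 0.0082 and the mean 0.0289. Two-sided alpha is 0.05. There are 50 clusters per arm, and 30,000 / 100 = 300 births per cluster ("each cluster will yield 300 births over 15 months"), so 15,000 births per arm. The printed ICC is 0.0245.

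**Assumptions, not in the article.** True correlation r of cluster rates between the earlier period and the trial: 0.5–0.8 as the central range, 0.3–1.0 as the wide range. Earlier births per cluster mb: 150–600.

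**Step 1: the stated sample size.** The individually randomised requirement for 90% power (two proportions, pooled variance under the null) is 8,770 per arm. Design effect DE = 1 + (300 − 1) × ICC.

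- ICC 0.0245: DE = 1 + 299 × 0.0245 = 8.33. The need is 8,770 × 8.3255 ≈ 73,015 births per arm, about 243 clusters. The planned 15,000 per arm are worth 15,000 / 8.3255 ≈ 1,802 independent births, which gives 31% power for the 25% reduction and 25% for the 22% reduction. The stated powers are not reproduced.
- ICC 0.00245: DE = 1 + 299 × 0.00245 = 1.73. The need is 8,770 × 1.73255 ≈ 15,194 per arm, 1.3% above 15,000. Power is 89.6% for the 25% reduction and 80.8% for the 22% reduction. Both stated powers are reproduced.

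The largest ICC at which 15,000 per arm gives 90% power is (15,000 / 8,770 − 1) / 299 ≈ 0.0024. Other readings fail: 255 births per cluster at the printed ICC gives 31% power, and treating 0.245 as a coefficient of variation gives 46 clusters per arm with 92% and 84% power.

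**Step 2: share of a cluster rate's variance that lies between clusters.** Share = 300 × ICC / DE.

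- ICC 0.0245: 7.35 / 8.3255 = 0.88.
- ICC 0.00245: 0.735 / 1.73255 = 0.42.

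The between-cluster standard deviation is √(ICC × 0.0289 × 0.9711), which is 26 per 1000 at the printed ICC and 8.3 per 1000 at the smaller one. Multiplying by √(2/50) gives the 5.2 and 1.7 per 1000 for the difference between arms.

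**Step 3: effect of the covariate.** A cluster-level covariate multiplies the variance by (1 − rho²), with rho = r × √(rel_b × rel_t). Here rel_t is the share from step 2, and rel_b = mb × ICC / (1 + (mb − 1) × ICC).

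| ICC | mb | r | rho | DE × (1 − rho²) | Power |
|---|---|---|---|---|---|
| 0.0245 | none | – | – | 8.33 | 31% |
| 0.0245 | 150 | 0.5 | 0.42 | 6.87 | 37% |
| 0.0245 | 300 | 0.8 | 0.71 | 4.17 | 55% |
| 0.0245 | 600 | 0.8 | 0.73 | 3.91 | 57% |
| 0.00245 | none | – | – | 1.73 | 89.6% |
| 0.00245 | 150 | 0.5 | 0.17 | 1.68 | 90.5% |
| 0.00245 | 300 | 0.8 | 0.34 | 1.53 | 92.8% |
| 0.00245 | 600 | 0.8 | 0.40 | 1.45 | 94.0% |

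Over the wide range of r (0.3–1.0), power runs from 33% to 94% at the printed ICC and from 89.9% to 96.1% at the smaller one.

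**The case against.** The strongest objection is that nothing here is wrong. A cluster-adjusted comparison with a random cluster effect is valid, its confidence interval already allows for chance differences between randomised clusters, and a fuller analysis plan may name more covariates. The point about validity stands. But the article does state an adjustment set for the primary comparison, so suggesting one more term is fair comment on what is written.

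Second, the covariate is inferred. A questionnaire that records only parity would not support it. This also stands, so the proposal has to be conditional. Even with suitable questions the measure is noisy: 300 births at 33 per 1000 yield about 10 deaths per cluster, and first-time mothers contribute none.

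Third, the covariate is not a true measurement before randomisation. It is recalled after unmasked allocation, and only by women who were found and consented. Pregnancy detection is described in detail for intervention clusters and as similar for control clusters. If the mix of enrolled women differed by arm, adjustment could distort the estimate. This stands and shapes the fix.

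A reader might also infer that between-cluster variance dominates the standard error and is left wholly untouched. The document does not support this. The 88% share holds only at an ICC that conflicts with the stated power; at the value that fits, it is 42%. Groundwater iron adjustment may remove some of the variance, by an amount that cannot be computed from the article, and stratifying allocation by Upazila limits geographic imbalance.

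**Conclusion.** The point holds as an efficiency suggestion. The stated primary comparison leaves out a prognostic cluster-level covariate that is probably available. At the ICC consistent with the protocol's own power figures, the gain is about 1 to 4 percentage points (89.6% to 90.5–94%). At the printed ICC it is about 5 to 26 points (31% to 37–57%), which under the central assumptions still falls well short of 90%. The covariate is therefore no remedy if 0.0245 is correct, and resolving that figure matters more than this point.

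The sizes rest on assumed values for the correlation over time and the number of earlier births, and on the questionnaire recording survival of earlier live births. It would be wrong to conclude that the planned analysis is biased, or that its inference fails to allow for arm differences that existed by chance before the trial.

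**What to change.** 1. Reconcile the ICC in the Sampling frame and sample size section with the stated power. The value of this change cannot be judged until that is done.
2. Check whether the reproductive history records earlier live births, neonatal deaths and dates. If it does not, drop the proposal.
3. If it does, prespecify before outcome data are examined by arm one cluster-level covariate in the primary comparison and in the Cox mixed model: the proportion of neonatal deaths among live births that occurred before the trial started.
4. Report the balance of this covariate by arm, and keep the analysis without it as a sensitivity analysis.

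The cost is one sentence in the analysis plan, one derived variable and one of about 98 between-cluster degrees of freedom, with no new data if the questionnaire is suitable. The downsides are recall error, no information from first-time mothers, and possible distortion if recruitment differs by arm.

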**Methods/design:**

The effect of the early use of iron-folic acid supplements on neonatal mortality will be examined using a community based, cluster randomised controlled trial in five districts with 30,000 live births. In intervention clusters trained BRAC village volunteers will identify pregnant women & provide iron-folic acid supplements. Groundwater iron levels will be measured in all study households using a validated test kit. The analysis will follow the intention to treat principle. We will compare neonatal mortality rates & their 95% confidence intervals adjusted for clustering between treatment groups in each groundwater iron-level group. Cox proportional hazards mixed models will be used for mortality outcomes & will include groundwater iron level as an interaction term in the mortality model.

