### Objectives and hypothesis

The trial objectives are to evaluate the effect of early availability and promotion of IFA supplements on neonatal mortality, low birthweight and preterm delivery. The primary hypothesis is that in a community-based, cluster randomized controlled trial of women from rural Bangladesh, daily supplementation with 60 mg elemental iron and 400 μg folic acid starting in the first trimester of pregnancy, and sustained for at least 180 days, will reduce neonatal mortality by 25% from 33/1000 to 24.8/1000 live births compared to usual iron-folic acid supplementation programs.

The secondary hypotheses are that the early availability and promotion of IFA supplements in intervention clusters will reduce preterm delivery by 30% (15% in control to 10.5% in intervention), and low birth weight by 30% (15% in control to 10.5% in intervention). We further hypothesised that household wealth and maternal education would modify the neonatal mortality responses with a greater reduction for women from the poorest households, and women with no education. We also hypothesised that the early start to IFA supplements would not increase iron-related side effects, e.g. nausea & vomiting in intervention clusters and will be cost-effective in reducing neonatal mortality in intervention clusters.

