#### Trial outcomes

The primary trial outcome will be the difference in the neonatal mortality rate between the intervention and control areas. The secondary trial outcomes will include: (1) percentage of women using IFA supplements in the first trimester of pregnancy; (2) percentage of live births with low birth weight and with preterm delivery; (3) percentage of neonatal deaths attributable to preterm delivery, and to birth asphyxia; (4) mean marginal additional expenditure associated with early IFA supplements, and the mean cost per neonatal death prevented; (5) the percentage of pregnant women reporting side effects including nausea and vomiting.

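### The abstract and the Methods describe different primary mortality comparisons, and the only named mortality model does not by itself return the overall effect the trial is sized for

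*Protocol article*

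**What the plan says.** **The target is one overall effect.** Objectives and hypothesis states that supplementation "will reduce neonatal mortality by 25% from 33/1000 to 24.8/1000 live births compared to usual iron-folic acid supplementation programs". Trial outcomes says: "The primary trial outcome will be the difference in the neonatal mortality rate between the intervention and control areas". Sampling frame and sample size sizes that single contrast "with 90% power, 5% two-sided alpha, 1:1 ratio of treatment allocation".

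**The analysis is described in two ways.**
- Abstract, Methods/design: rates and intervals are compared "adjusted for clustering between treatment groups in each groundwater iron-level group". This is a separate comparison of arms at each iron level, with no primary or secondary label.
- Statistical analysis: "The primary analyses will compare the neonatal mortality rates and their 95% confidence intervals adjusted for clustering and groundwater iron level in each group". This is an adjusted comparison, and the section does not say whether the final word refers to treatment arms or to iron groups.

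**One regression model is named for mortality.** After a sentence introducing mixed models as secondary analyses, the Statistical analysis section says: "We will use Cox proportional hazards mixed models for mortality outcomes and include groundwater iron level as an interaction term in the mortality model". The abstract describes the same model without calling it secondary. The section adds that the models will assess change over time by "testing for an interaction between time and intervention group".

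The Groundwater iron section says that iron is measured in every study household. It gives no cut-points, number of groups or expected shares.

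**The concern.** Adjusting for a factor and estimating the effect separately at each of its levels answer different questions. The first gives one treatment effect; the second gives as many as there are iron groups, each from part of the data. The trial is sized only for the first.

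The named model does not settle the matter. Once treatment by iron is in the model, the treatment coefficient is the effect in the reference iron category, or at 0 mg/L if iron is continuous. Changing the reference changes the coefficient. As an invented illustration, if the true reduction were 40% in low-iron and 10% in high-iron households, the coefficient labelled treatment could show either figure.

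The intervention cannot be masked (Assignment of treatments). Leaving more than one candidate for the headline result therefore allows a choice after the data are seen, and some of the candidates have much less power than planned.

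**Working it through.** **Step 1. The passages side by side.**

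| Place | Contrast | Effects produced |
|---|---|---|
| Objectives; Trial outcomes; Sample size | Intervention vs control, overall | One |
| Abstract, Methods/design | Arms within each iron group | One per iron group |
| Statistical analysis, primary sentence | Rates adjusted for clustering and iron, group undefined | One if group means arm; several if it means iron group |
| Statistical analysis, Cox sentence | Treatment with iron interaction | Reference-level effect plus interaction terms |

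No mortality model without the interaction is stated, and no rule for averaging over iron levels.

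**Step 2. The plan's own sample size.** Inputs from Sampling frame and sample size: 33 vs 24.8 per 1000, two-sided 5%, 90% power, 50 clusters per arm, 30,000 births (300 per cluster), and "intra-cluster correlation coefficient (ICC) of 0.0245". The two-proportion formula gives 8,770 births per arm before clustering. At the printed ICC the design effect is 1 + 299 × 0.0245 = 8.33. That requires 8,770 × 8.33 / 300 ≈ 243 clusters per arm, and 50 per arm gives about 31% power. The stated figure is not reproduced at the printed ICC. That is a separate matter. For the present point I take the stated 90% as given, which implies a design effect of 15,000 / 8,770 = 1.71, or an ICC of (1.71 − 1) / 299 ≈ 0.0024.

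**Step 3. Power within one iron group.** Let f be the assumed share of births in the group. The planned standardised effect is 1.960 + 1.282 = 3.242. Two extremes bracket the clustering.

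- *Iron groups coincide with whole clusters.* The design effect stays at 1.71, so z = 3.242 × √f and power = Φ(z − 1.960).
- *Iron levels spread evenly within every cluster.* Each cluster contributes 300f births to the group, so the design effect falls to 1 + (300f − 1) × 0.0024 and z = 3.242 × √(f × 1.71 / new design effect).

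| Share f | z, whole clusters | Power | Design effect, spread evenly | z, spread evenly | Power |
|---|---|---|---|---|---|
| 0.50 | 2.29 | 63% | 1.35 | 2.58 | 73% |
| 0.30 | 1.78 | 43% | 1.21 | 2.11 | 56% |
| 0.20 | 1.45 | 30% | 1.14 | 1.78 | 43% |

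All six values are well below 90%. The same power applies to testing the treatment coefficient of an interaction model when the reference category holds share f.

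**Step 4. Power for the interaction itself.** With two groups, its standard error is the overall one divided by √(f(1 − f)), which doubles it for equal halves. Keeping the overall design effect, an interaction as large as the sized main effect has z = 3.242 / 2 = 1.62 and power of about 37%.

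**The case against.** A reader might infer that no stated analysis estimates the overall effect. The documents do not support that. The primary sentence in Statistical analysis comes before any model is named. The article uses treatment group for the arms, so the natural reading is an overall comparison of arms adjusted for clustering and iron, which matches the hypothesis, outcome and sample size. The Cox model follows the sentence on secondary analyses and is most naturally one of them.

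Nor does it follow that the primary hypothesis has no 5% test. The sample size section sets a two-sided 5% level for the overall contrast. Testing a time-by-treatment term does not make it part of the primary estimate. An interaction model can also yield an overall effect by averaging over iron levels, and coding, cut-points and averaging are details that an article may leave to the full analysis plan. No passage says that the reference-level coefficient will be reported as the trial result.

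These points stand, and they limit the finding. They do not remove it. The abstract explicitly compares arms within iron groups and presents the interaction model without a secondary label. The primary sentence leaves its last word undefined and names no estimator. This is a conflict between two statements about the primary comparison, so it is more than omitted detail: an analysis plan that followed the overall reading would have to depart from the abstract.

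**Conclusion.** The point holds as an inconsistency. The overall contrast is what the trial defines and sizes, and the Methods probably intend it. The abstract describes a different, stratum-specific comparison, and the only named mortality model does not return the overall effect through its treatment coefficient.

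If the abstract were followed, power for the sized 25% reduction would fall from the planned 90% to about 63–73%, 43–56% or 30–43% in a group holding 50%, 30% or 20% of births. The lower value applies if iron groups align with whole clusters, the higher if they are spread evenly within clusters. These figures are illustrative: the shares are assumed, the reduction is taken as uniform across iron levels, and the stated 90% is accepted although the printed ICC does not reproduce it. That the contrasts differ, and that the coefficient depends on coding, needs none of these assumptions.

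**What to change.** State one primary analysis: the overall intervention-versus-control contrast in neonatal mortality, by intention to treat, adjusted for clustering, the Upazila randomisation stratum and groundwater iron as a main effect only. Averaging the treatment effect over the observed iron distribution would serve equally well. Name the effect measure and estimator, with one 95% confidence interval and one two-sided 5% test.

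Label treatment by groundwater iron and treatment by time as separate secondary models, and take iron-group-specific estimates from the former. Reword the abstract to match, and replace the undefined reference to each group in the primary sentence with treatment arm.

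The cost is a few sentences in the protocol and analysis plan, and at most one extra model fit. Data collection and sample size do not change, and the question of whether groundwater iron modifies the effect is kept in full.

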### Study setting

We will conduct the Shonjibon trial in five districts in Dhaka Division, Bangladesh. These districts are Netrokona, Kishoreganj, Mymensingh, Sherpur, and Gazipur, with a total number of 47 Upazila (subdistricts) and a combined population of 20 million. Our study implementing partner BRAC, a non-government organisation co-ordinates a community-based maternal, neonatal and child health program in the area which includes a prospective pregnancy surveillance and home-based antenatal care program. The Shonjibon study area will consist of 24 Upazilas from these five districts (Fig. 1). We will exclude five Upazilas from Kishoreganj, six Upazilas from Netrokona and two Upazilas from Sherpur because of insufficient BRAC Program Officer (PO) coverage. We will also exclude three Upazilas from Gazipur because of the high number of garment industries, which would have high numbers of working women and would be difficult to follow-up and eight Upazilas from Mymensingh because of the high prevalence of malaria and kalazar.

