### Assignment of treatments

An investigator remote from the field area will assign the interventions to eligible clusters using a fixed randomisation scheme with a uniform allocation ratio of treatments, stratified by subdistrict or Upazila. The random allocation sequence will be generated using Stata 12 software (StataCorp. 2011. Stata Statistical Software: Release 12. College Station, TX: StataCorp LP). The nature of the intervention precludes the masking of the treatments.

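### Cluster allocation is stratified by Upazila, but the described models have no Upazila term; if mortality differs between Upazilas, standard errors are somewhat too large

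*Protocol article*

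**What the plan says.** Under Assignment of treatments, the protocol article allocates clusters by a "fixed randomisation scheme with a uniform allocation ratio of treatments, stratified by subdistrict or Upazila". Study setting gives the number of strata: "The Shonjibon study area will consist of 24 Upazilas from these five districts".

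The Statistical analysis section names these model terms:

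- For the primary comparison: "The primary analyses will compare the neonatal mortality rates and their 95% confidence intervals adjusted for clustering and groundwater iron level in each group".
- For the Cox mixed models, the plan is to "include groundwater iron level as an interaction term in the mortality model".
- For the models generally: "Models will include treatment group as a fixed effect, community-cluster as a random effect to account for the cluster effect".
- An interaction between time and intervention group, and subgroup analyses by wealth, infant sex and maternal education.

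Neither Upazila nor the stratification of the allocation is mentioned in that section.

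**The concern.** Stratified allocation balances the arms within each Upazila, so mortality differences between Upazilas largely cancel out of the treatment contrast. A model with only a treatment effect and a cluster random effect does not know this. It pools the between-Upazila variance into the cluster variance and charges it to the standard error of the treatment effect. The estimate is as precise as the design made it, but the analysis reports it as less precise.

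The consequence is intervals that are too wide, a type I error below the nominal 5%, and some loss of power. In a superiority trial on mortality, the price is a greater chance of missing a real effect. The same applies to preterm delivery and low birth weight if they vary by Upazila.

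**Working it through.** **Inputs from the article.** Control and intervention rates: "33 neonatal deaths/1000 live births in control to 24.8 neonatal deaths/1000 live births in the intervention group". Size: 100 clusters, "or 50 clusters per treatment group, with a total of 30,000 live births over one year", so 300 births per cluster. Power 90%, two-sided 5%, 1:1, printed ICC 0.0245. Strata: 24.

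**Assumption.** Let f be the share of between-cluster variance that lies between Upazilas and is not explained by groundwater iron. The article gives no value, so a range is shown.

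**Step 1: reproduce the planned size.** The two-proportion formula for 33 vs 24.8 per 1000 gives 8,770 per arm before clustering. The design effect is 1 + (300 − 1) × ICC.

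- ICC 0.0245 (printed): 1 + 299 × 0.0245 = 8.33, so 8,770 × 8.3255 = 73,015 per arm, 146,029 in total. With 15,000 per arm, power is about 31%. The stated size is not reproduced.
- ICC 0.00245: 1 + 299 × 0.00245 = 1.73, so 8,770 × 1.73255 = 15,194 per arm, 30,389 in total. With 15,000 per arm, power is 89.6%, and 80.8% for a 22% reduction. Both stated power figures are matched.

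The rest uses 0.00245 because it is the value consistent with the planned size. The mismatch with the printed value is a separate and larger point.

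**Step 2: variance of a cluster rate.** Mean rate (0.033 + 0.0248)/2 = 0.0289; binomial variance 0.0289 × 0.9711 = 0.028065.

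- Between clusters: 0.00245 × 0.028065 = 0.00006876.
- Within clusters: 0.028065 × (1 − 0.00245)/300 = 0.00009332.

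**Step 3: reported and true standard error.** With 50 clusters per arm the multiplier is 1/50 + 1/50 = 0.04.

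- Reported without Upazila: √[(0.00006876 + 0.00009332) × 0.04] = 0.002546, whatever f is.
- True, and reported with Upazila: √[(0.00006876 × (1 − f) + 0.00009332) × 0.04].

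**Step 4: power.** The difference is 0.033 − 0.0248 = 0.0082. Without Upazila (98 df, critical value 1.984), power is Φ[(0.0082 − 1.984 × 0.002546)/true SE]. With Upazila (100 − 24 − 1 = 75 df, critical value 1.992), power comes from the non-central t with non-centrality 0.0082/true SE.

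| f | True SE | Reported SE too large by | Power without Upazila | Power with Upazila |
|---|---|---|---|---|
| 0 | 0.002546 | 0% | 0.892 | 0.889 |
| 0.10 | 0.002492 | 2% | 0.897 | 0.901 |
| 0.25 | 0.002407 | 6% | 0.904 | 0.920 |
| 0.50 | 0.002260 | 13% | 0.918 | 0.948 |
| 0.75 | 0.002102 | 21% | 0.933 | 0.971 |

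Power without Upazila also rises with f, because the stratified allocation shrinks the true variance whether or not the model uses it.

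**Step 5: simulation.** 4,000 trials per scenario; 24 strata (20 of four clusters, 4 of five); stratified allocation; cluster-level analysis without vs with Upazila fixed effects; ICC 0.00245.

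| f | Type I error, without vs with | Power, without vs with |
|---|---|---|
| 0 | 0.055 vs 0.057 | 0.90 vs 0.89 |
| 0.25 | 0.040 vs 0.052 | 0.90 vs 0.92 |
| 0.50 | 0.028 vs 0.056 | 0.92 vs 0.94 |

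The Monte Carlo standard error of a power near 0.90 is √(0.9 × 0.1/4000) ≈ 0.005. Simulation and formula agree in direction and approximate size.

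**Sensitivity to the ICC.** At the printed 0.0245, simulated power without vs with Upazila is 0.30 vs 0.29 (f = 0), 0.24 vs 0.31 (f = 0.25) and 0.22 vs 0.38 (f = 0.50). The effect of the stratum would be larger, but the trial would be badly underpowered either way.

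**The case against.** The strongest reply is that nothing in the article excludes Upazila. The sentence on model content is not a closed list: the same section adds groundwater iron and time terms, and it allows adjustments after checking assumptions. The article is condensed, and an analysis plan that is not shown may contain the term. That stands as a caution, and the point should not be read as saying that Upazila has been ruled out. It does not dispose of the point. The section names each adjustment it intends, and the one factor that constrained the allocation is absent. Followed as written, the models do not match the design.

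A second reply is that the loss may be nil. This is correct if Upazilas do not differ, and groundwater iron, which varies by area, may absorb part of any difference. It is unlikely to be a full substitute, being one household measurement and not the design stratum.

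A reader might infer that precision is certainly lost, or that the whole benefit of stratifying is discarded. The article supports neither. It gives no between-Upazila variance, and unadjusted power also gains from stratified allocation. At a 50% share the fair comparison is 0.918 with 0.948, about 3 points, and not 0.90 with 0.95. The planned 90% power also states no allowance for stratification, so it does not depend on this adjustment.

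**Conclusion.** The mismatch is real: allocation is stratified by Upazila and the described models do not use the stratum. The consequence is conditional. For an Upazila share of 25% to 50% of between-cluster variance at ICC 0.00245, the reported standard error is 6% to 13% too large and about 2 to 3 power points are forgone. With no Upazila variation nothing is lost. Both the share and the ICC are assumptions.

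It would be wrong to conclude that the trial's inference is invalid. The error is conservative: it introduces no bias and does not inflate the type I error. This is a cheap improvement and not a defect that endangers the conclusions.

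**What to change.** Add one sentence to the Statistical analysis section stating that Upazila enters the primary and secondary arm comparisons:

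- Cox models: stratify the baseline hazard by Upazila, or include Upazila fixed effects.
- Poisson models: include Upazila effects.
- In both: keep the cluster random effect or cluster-level variance, since Upazila does not replace the cluster.

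If Upazila is to be left out, give the reason. Either way, fix the choice before outcome data by arm are seen.

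No new data are needed. The cost is 98 − 75 = 23 cluster-level degrees of freedom. If Upazilas do not differ, that is roughly 0.3 power points by the formula (0.892 vs 0.889) and about 1 point in the simulation (0.90 vs 0.89).
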